***Background***

It has been estimated that more than one third the world's population is infected with one or several species of parasitic worms and that in the Indian subcontinent, there were 160 million cases of ascariasis and hookworm infestation each. The consequences of such infestations are malnutrition and anemia. Infestation begins from the time children are weaned, around the age of six months, and by the time they reach the school going age helminths are the leading cause of disability. The critical period for malnutrition is between 6 months to 24 months of age, which also coincides with the period where worm infestations begin. The most appropriate period, then, to tackle malnutrition, and thereby reduce malnutrition related mortality, is in the preschool age group. In this age, it has been estimated that 42-57% of deaths are due to malnutrition's potential effects on infectious diseases, of which 76-89% is attributed to mild-to-moderate malnutrition.

A number of studies have identified an improvement in nutritional status following deworming treatment, but it is evident that findings vary. Some trials have reported significant improvements in growth, whereas others have failed to detect a change.

We, therefore, conducted a randomized trial to study of the effects of albendazole on growth in preschool children . Our study hypothsis was that albendazole administration six monthly, as a single 400 mg dose in syrup, by the existing health care delivery system would be a practicable way to achieve mass deworming of preschool children and this might result in an improvement in weight gain of preschool children.

# Review of Literature

**Parasitic worms** (helminths) are a common cause of chronic infection in humans. This review concerns the effects of deworming for soil-transmitted worms only, and does not cover schistosomiasis. World Bank estimates in 1993 ranked soil-transmitted worms first in terms of global burden of disease in the 5-14 year age group (World Bank 1993). Global estimates suggest that more than a quarter of the world’s population are infected with one or more of the most common soil-transmitted intestinal worms (nematode geohelminths) (Chan 1997). These include roundworms (Ascaris lumbricoides), hookworms (Necator americanus and Ancylostoma duodenale) and whipworms (Trichuris trichura). Most infected people harbour multiple species. Infections are widely distributed in tropical and sub-tropical areas. The burden of disease falls disproportionately on the poor, where inadequate sanitation, overcrowded conditions, low levels of education and lack of access to health make them particularly susceptible.

The distribution of worms in mammalian hosts is highly skewed. In a population certain people harbour particularly high worm burdens, whereas others carry just a few parasites. Studies have also shown a correlation between individual pre-treatment worm intensity and that attained on re-infection after treatment. This may reflect differences in exposure and susceptibility to infection, and variations in worm survival. Children are more at risk of high worm burdens, with peak intensities at 5-10 years for roundworms and whipworms. Hookworm burden peaks later.

Roundworms obtain their nutrition from gastrointestinal contents. There is an association with malnutrition, possibly mediated through impaired fat digestion, reduced vitamin absorption (particularly vitamin A) and temporary lactose intolerance (WHO 2002). Whipworm infection has also been associated with malnutrition, the precise mechanism for this being unclear (Cappello 2004). Suggested mechanisms for worm effects on growth include appetite suppression, increased nutrient loss, and decreased nutrient absorption and utilisation (Stephenson 2000, deSilva 2003).

**Albendazole:** The drugs that have been used in the current decade for mass deworming are mebendazole and albendazole (1,16). Albendazole is a benzimidazole derivative and has a broad spectrum antihelminthic effect (16). We have used albendazole because it is usually administered in a single dose. It is so safe that it can be used by non-mediacl personnel within a program. The cure rates of 400 mg of the drug in subjects of all ages and those between 2 to 14 years of age is 100% for ascariasis (17,18) and 63 to 84% for hookworms, the two different cure rates are based on the technique for identification of the hookworms (18). The drug has been used in children less than 2 years of age without any significant side effects (19).

Albendazole is being used for school based deworming programs where the measure of effectiveness is gain in weight. With albendazole, we have demonstrated weight gain even in the preschool children.

## Design

### Study Hypothesis

. Our study hypothsis is that albendazole administration six monthly, as a single 400 mg dose in syrup, by the existing health care delivery system would be a practicable way to achieve mass deworming of preschool children and this might result in an improvement in weight gain of preschool children.

### Objectives

Primary objective:

1. To assess the impact of 6 monthly deworming on weight and height gain at the end of 2 years in children aged 1 to 5 years of age

### Setting

The study will be conducted in urban slums of Lucknow, a heavily populated area of North Central India. There is one slum, or *'anganwadi'* for a population of approximately 1000 economically disadvantaged persons. The criteria for selecting an area for an urban slum are that it does not have the basic amenities of sanitation and water supply and the income of its residents is below the national poverty level. To ensure primary health care of children under five years of age, all the urban slums in Lucknow are covered by the national Integrated Child Development Scheme (ICDS). Through the ICDS, there is one informal health worker, the *'anganwadi'* worker per slum and the entire slum population is registered with her. There are 203 slums within urban Lucknow. These will be listed alphabetically and given a serial number. After generating a random digit table with 55 number, the first slum will be randomized to either one intervention type by toss of coin, and then every alternate slum having the same serial number as that in the random digit table will receive this intervention, the rest the other. Thus, 50 slums will be randomly allocated, 25 to each of the two arms of the trial.

### Design

This study will be a cluster randomized open labeled trial within the existing health care infrastructure. It will be conducted after clearance from the local institutional ethics committee.

### Intervention

One group will received usual health care by the existing health care staff, which included six monthly administration of Vitamin A concentrate. The other group will receive, in addition, 400 mg of albendazole (Zentel, Smith Kline & Beecham) in 10 ml syrup form. Five such doses will be given given at six monthly intervals for 2 years.

### Unit of randomization

Randomization will be by the urban slums.

### Selection of Subjects

All the children residing in the slums and between 1 through 5 years of age will be invited for participation in the study, after obtaining written consent from the parents. The date of birth of children was noted from the register maintained by the slum health workers.

### Variables

The main outcome measures are weight and height. The project workers will measure these on the day of the visit, once every six months. To ascertain age of the hild, date of birth will be abstracted from the register of the '*anganwadi'* worker. For those who cannot be contacted at the time of the visit but were not reported as dead, a second visit will be made to ascertain the reason for loss to follow-up. Parents of dead children will be contacted to ascertain the cause of death.

The weight of the child will be measured in kilograms to the nearest 100 grams and the standing height was measured in centimeters to the nearest millimeter. It will not be possible to blind the data collectors or the parents to the intervention type. However, the data collectors did not have information of the previous weight or height of the children. Approximately 10% of the data will be validated by different project workers within 1 week. The validators will be blind to all the anthropometric data on the subjects.

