### Compliance

The project staff themselves will administer the intervention. Independent data collectors will validate this in 10% children within 15 days. Empty bottles of intervention will be retained and counted. The numbers of empty bottles and the doses within them will be compared with the doses administered.

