### Sample Size and Data Analyses

Sample Size: Sample size was calculated for a continuous outcome. For a standardized effect size of 0.1, with a power of 80% and an alpha level of 0.05, using a 2-tailed t test, taking into account design effect, about 2000 children will be included in each arm.

Data Analysis:EPI6.1 statistical software will be used to calculate at baseline, weight for age (WA), height for age (HA) and weight for height (WH) z scores, when compared to the nutritional standards of the World Health Organization. Baseline distribution of undernutrition (weight for age (WAZ) z score < - 2 standard deviations (S.D.)), stunting (height for age (HAZ) z score < - 2 S.D.) and wasting (weight for height (WHZ) z score < - 2 S.D.) will be calculated for all the enrolled children. Weight by age will be calculated for all the enrolled children using the 1994 data of the first survey. Univariate analyses will be done to compare age, sex and history of passage of worms and weight and height in 25 control areas and 25 albendazole areas using the chi square test for categorical and student's t test for continuous variable.

Because randomization will be by area, we will assess the area specific weight gain and height gain in each group. We will report area specific averages, taking one result per area. Height and weight gain in one year and two years will be compared in 25 control versus 25 albendazole areas.

In subgroup analysis, weight and height gains will be calculated for children who are underweight, stunted and wasted at enrollment in the control and ABZ groups. We will also compare 2-year changes in the proportion of underweight, stunted and wasted in the two groups.

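### Gain is not scaled to the actual measurement interval and visit order need not be balanced by arm, which adds avoidable noise and leaves a route to bias against a 0.1 SD target

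*Protocol*

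**What the plan says.** - **Timing of measurement** (Protocol, Variables): "The project workers will measure these on the day of the visit, once every six months". The section gives no visit window and no order or calendar for visiting slums.
- **Comparison** (Protocol, Sample Size and Data Analyses): "Height and weight gain in one year and two years will be compared in 25 control versus 25 albendazole areas", with one average per area. The text does not scale gain to the actual interval or reference it to age. Z scores are specified at baseline. The only follow-up comparison with an age reference is the change in the proportions underweight and stunted.
- **Dosing** (Protocol, Compliance): "The project staff themselves will administer the intervention". Bottles are counted and administration is checked in a tenth of children. The syrup is given in one arm only, and the trial is open label.
- **Size** (Protocol, Setting; Sample Size and Data Analyses): "50 slums will be randomly allocated, 25 to each of the two arms of the trial". The target is set as "For a standardized effect size of 0.1, with a power of 80% and an alpha level of 0.05", and the calculation continues "using a 2-tailed t test, taking into account design effect, about 2000 children will be included in each arm".

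**The concern.** Raw gain rises roughly in proportion to the time between the first and last weighing. Fifty slums and about 4000 children per round will hardly be covered on one day, so actual intervals will vary around 12 and 24 months. Two consequences follow.

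1. Interval variation between slums inflates the variance of the area averages and costs power.
2. If the mean first-to-last interval differs between arms, that difference adds directly to the effect estimate and looks the same as an effect of albendazole. The extra dosing and bottle accounting in one arm is a conceivable cause.

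Both matter more than usual here because the effect sought is only a tenth of an SD.

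**Working it through.** **Inputs from the Protocol:** target 0.1 SD, two-sided alpha 0.05, power 80%, about 2000 children per arm, 25 slums per arm. The design effect, ICC, growth rate and SD of gain are not stated.

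**Step 1, the plan's own figure.** Without clustering, n per arm = 2 × (1.960 + 0.842)² / 0.1² = 1570. The stated 2000 cannot be reproduced because no design effect is given. Solving backwards, 2000/1570 = 1.27. With 2000/25 = 80 children per slum, the implied ICC is (1.274 − 1)/79 = 0.0035.

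**Step 2, interval difference equal to the target.** Weeks = 0.1 × SD of 2-year gain / weekly growth, with weekly growth = yearly growth / 52.18. All growth figures below are assumptions.

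| Outcome | Growth per year | SD of 2-year gain | Weeks equal to 0.1 SD |
|---|---|---|---|
| Weight | 2.0 kg | 0.75 to 1.5 kg | 2.0 to 3.9 |
| Weight, wider | 1.5 to 2.5 kg | 0.75 to 2.0 kg | 1.6 to 7.0 |
| Height | 7 cm | 3 to 5 cm | 2.2 to 3.7 |
| Height, wider | 6 to 10 cm | 2 to 5 cm | 1.0 to 4.3 |

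Example: 0.1 × 0.75 / (2.0/52.18) = 2.0 weeks. The overall range is about 1 to 7 weeks.

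**Step 3, could chance alone produce such a difference?** If slum intervals have SD s, the SE of the difference between arm means is s × √(2/25).

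- s = 2 weeks: SE = 0.57 week. A difference of 2 weeks or more has probability about 0.0004.
- s = 4 weeks: SE = 1.13 weeks. The probability is about 0.08.

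A bias as large as the target therefore needs a systematic cause tied to arm, unless intervals are very loose.

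**Step 4, cost as noise.** The variance of the arm difference implied by the plan is 2 × 1.274/2000 = 0.001274 (in SD²), so 0.1/√0.001274 = 2.80 and power is 80%. Interval variation adds 2v/25, where v = (0.1 × s/w)² and w is the number of weeks that equal 0.1 SD.

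| s (weeks) | w (weeks) | v | Variance of difference | Power |
|---|---|---|---|---|
| 1 | 4 | 0.000625 | 0.001324 | 78% |
| 1 | 2 | 0.0025 | 0.001474 | 74% |
| 2 | 4 | 0.0025 | 0.001474 | 74% |
| 2 | 2 | 0.0100 | 0.002074 | 59% |

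For s = 2 weeks the added between-slum variance is 0.7 to 2.9 times the 0.0035 that the plan implies. This uses a normal approximation, an assumed s, and the premise that the plan's design effect does not already include interval variation.

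**The case against.** - **Silence is not imbalance.** A reader might infer that visit order is unbalanced by arm, or that the arms' schedules will drift apart. The Protocol says neither; it simply does not require balance. This objection stands.
- **The dosing mechanism largely cancels.** Five six-monthly doses over two years, if the first is given at baseline, fall at months 0, 6, 12, 18 and 24. The extra work is then present at the first and last rounds alike, and a constant slowdown leaves the interval unchanged. Bias needs a burden that changes between rounds, and no such change is documented. Nor does the text say outright that the people who dose are the people who measure. This also stands, and it is the main reason not to claim bias.
- **Season.** Visits 12 or 24 months apart begin and end in the same season, so a seasonal bias would again require arm-specific drift.
- **Chance variation is handled by the design.** With slums randomized and one result per area, it enters the error term and does not bias the estimate. That is correct, but the power cost in step 4 remains.
- **The 2 to 4 weeks is not in the Protocol.** It depends on assumed growth figures. The text also does not say that the 0.1 is standardized by the SD of gain; a larger SD would lengthen the equivalent drift.
- **Date scaling may sit in an analysis plan that is not shown.** This is fair for the scaling and for reporting intervals. It does not cover visit order: once fieldwork is done, no analysis plan can restore a balanced roster.

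**Conclusion.** The point holds as a cheap improvement; it is not a demonstrated bias. As written, variation in interval between slums goes straight into the outcome, and nothing prevents an arm-linked difference in interval. The power losses in step 4 hold only if slum intervals really vary with an SD of 1 to 2 weeks and the implied design effect of 1.27 leaves that variation out. The equivalence between weeks of drift and the target should always be quoted with its assumptions and its full range. Only a difference between arms in the first-to-last interval biases the estimate; a delay common to both arms, or a fixed visit order, does not.

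**What to change.** 1. In the Protocol, require an arm-balanced visit order in every round: one control and one albendazole slum in the same week, in the same order each round.
2. Record the date of every measurement. Compute each child's gain from the actual dates, scaled to 24 months (gain × 730 / days elapsed) or, for the one-year comparison, to 12 months (gain × 365 / days elapsed), before averaging by area.
3. Report the mean measurement interval by arm.

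The cost is a visit roster and one line of calculation on dates of visits that are made anyway. Field teams lose some freedom in routing. Linear scaling is only approximate across ages 1 to 5 and does not correct for season, but it is adequate for deviations of a few weeks.

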### Compliance

The project staff themselves will administer the intervention. Independent data collectors will validate this in 10% children within 15 days. Empty bottles of intervention will be retained and counted. The numbers of empty bottles and the doses within them will be compared with the doses administered.

### Sample Size and Data Analyses

Sample Size: Sample size was calculated for a continuous outcome. For a standardized effect size of 0.1, with a power of 80% and an alpha level of 0.05, using a 2-tailed t test, taking into account design effect, about 2000 children will be included in each arm.

Data Analysis:EPI6.1 statistical software will be used to calculate at baseline, weight for age (WA), height for age (HA) and weight for height (WH) z scores, when compared to the nutritional standards of the World Health Organization. Baseline distribution of undernutrition (weight for age (WAZ) z score < - 2 standard deviations (S.D.)), stunting (height for age (HAZ) z score < - 2 S.D.) and wasting (weight for height (WHZ) z score < - 2 S.D.) will be calculated for all the enrolled children. Weight by age will be calculated for all the enrolled children using the 1994 data of the first survey. Univariate analyses will be done to compare age, sex and history of passage of worms and weight and height in 25 control areas and 25 albendazole areas using the chi square test for categorical and student's t test for continuous variable.

Because randomization will be by area, we will assess the area specific weight gain and height gain in each group. We will report area specific averages, taking one result per area. Height and weight gain in one year and two years will be compared in 25 control versus 25 albendazole areas.

In subgroup analysis, weight and height gains will be calculated for children who are underweight, stunted and wasted at enrollment in the control and ABZ groups. We will also compare 2-year changes in the proportion of underweight, stunted and wasted in the two groups.

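### The stated 80% power for 0.1 SD holds only if the intra-slum correlation is about 0.003 or less with no 2-year loss, and the protocol states neither quantity

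*Protocol*

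**What the plan says.** The Sample Size and Data Analyses section of the protocol gives the target difference ("For a standardized effect size of 0.1") and the error rates ("with a power of 80% and an alpha level of 0.05", two-tailed t test). It concludes that, "taking into account design effect, about 2000 children will be included in each arm". It gives no numerical design effect, no ICC and no allowance for loss.

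The clusters are fixed elsewhere. Under Unit of randomization: "Randomization will be by the urban slums". Under Setting: "Thus, 50 slums will be randomly allocated, 25 to each of the two arms of the trial". The planned comparison follows the randomization: "We will report area specific averages, taking one result per area". The primary objective is gain in weight and height after 2 years, and the Variables section foresees children who cannot be found: "a second visit will be made to ascertain the reason for loss to follow-up".

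**The concern.** The sample size is expressed in children, but with one result per area the information in the trial is limited by 25 slums per arm. The margin between the number needed without clustering and the 2,000 stated is small, and it has to cover both the similarity of children within a slum and losses over 2 years. If either is more than slight, power for 0.1 SD falls below the stated 80%. A null result could then be read as showing that deworming does not improve growth, when the trial had limited ability to detect the difference it was sized for.

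**Working it through.** **Inputs.** From Sample Size and Data Analyses: difference d = 0.1 SD (read as the SD of individual children's gain), two-sided alpha 0.05, power 80%, about 2,000 children per arm, one mean per area. From Setting: k = 25 slums per arm. Hence m = 2000/25 = 80 children per slum and 2 × 25 − 2 = 48 degrees of freedom. ICC and loss are not in the protocol, so every value used for them below is an assumption.

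**Step 1: the plan's own figure.** Without clustering, n per arm = 2(1.960 + 0.842)²/0.1² = 1,570, or 1,571 with the t distribution. The 2,000 cannot be reproduced further, because the design effect used is not stated. The implied total inflation is 2000/1571 = 1.27. Reading about 2,000 as 1,950 to 2,050 gives 1.24 to 1.31.

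**Step 2: what 1.27 allows.** If all of it goes to clustering, 1 + (80 − 1) × ICC = 1.27 gives ICC = 0.27/79, about 0.0035, with nothing left for loss. If 2,000 is counted at enrolment, 10% loss leaves 1,800/1,571 = 1.15 and 20% loss leaves 1,600/1,571 = 1.02.

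**Step 3: the planned analysis.** The variance of an area mean, in SD² units, is V = ICC + (1 − ICC)/m. The standard error of the difference is √(2V/25). With 48 df, 80% power needs 0.1/√(2V/25) to be about 2.859, so V must be at most 25 × 0.1²/(2 × 2.859²) = 0.0153. Solving for ICC = (0.0153 − 1/m)/(1 − 1/m), with V carried unrounded as 0.01529:

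| Children per slum analysed | 1/m | Largest ICC for 80% power |
|---|---|---|
| 80 (no loss) | 0.0125 | 0.0028 |
| 72 (10% loss) | 0.0139 | 0.0014 |
| 64 (20% loss) | 0.0156 | none; power is 79% at ICC 0 |
| 125 (assumed larger yield, no loss) | 0.0080 | 0.0073 |
| Unlimited | 0 | 0.0153 |

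The last row means that with 25 slums per arm and an ICC above 0.0153, no number of children per slum reaches 80% power for 0.1 SD.

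**Step 4: power for 0.1 SD over an assumed ICC range** (noncentral t, 48 df):

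| ICC | No loss (m = 80) | 20% loss (m = 64) |
|---|---|---|
| 0.001 | 85% | 77% |
| 0.002 | 82% | 74% |
| 0.005 | 75% | 68% |
| 0.01 | 64% | 58% |
| 0.02 | 49% | 45% |
| 0.05 | 29% | 27% |

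Example: at ICC 0.01 with no loss, the design effect is 1 + 79 × 0.01 = 1.79, the standard error is √(2 × 1.79/2000) = 0.0423, and 0.1/0.0423 = 2.36, which gives 64%.

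**Step 5: detectable difference at 80% power with 20% loss.** It is 2.859 × √(2 × design effect/1600). At ICC 0.01 the design effect is 1 + 63 × 0.01 = 1.63, giving 0.13 SD. At ICC 0.02 it is 2.26, giving 0.15 SD.

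**The case against.** A reader might infer that 80% power is simply not delivered by 25 versus 25 slums. The protocol does not support that, because it gives no ICC and no loss rate. With no loss, power is 85% at ICC 0.001 and 82% at 0.002, and with 10% loss and ICC 0.001 it is 81%. The design effect the investigators used is undisclosed, not shown to be wrong. This objection stands, and the point is worded as a condition for that reason.

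It is also fair to say that the 2,000 is not explicitly an enrolment figure. All eligible children in the slums are invited, without a cap, and a slum has about 1,000 residents, so intake could exceed 80 per slum. At an assumed 125 per slum the tolerable ICC rises to about 0.007, and even with 20% of those lost (100 left) power at ICC 0.005 is 81%. That widens the room but does not remove the condition: at ICC 0.01 and 125 per slum with no loss, power is about 73%. Nor is 20% loss a protocol figure; the Variables section says how losses will be followed up, not how many are expected.

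Finally, the planned comparison respects the unit of randomization, so type I error is not in question. What remains is that the protocol makes an unqualified power statement and says clustering was allowed for. Testing that statement against its own inputs is not a request for detail that belongs in an analysis plan.

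**Conclusion.** The point holds as a conditional statement. The margin of 1.27 for clustering and loss together follows from the protocol's own figures and does not depend on how about 2,000 is rounded. On the planned area-level comparison with 80 children per slum, the stated power needs near-zero clustering and little loss. Even with zero ICC, 80% requires about 65 children analysed per slum (1/0.0153), so a loss of more than about 18% from 80 breaks it. How far power actually falls below 80%, if it does, cannot be determined from the protocol. The range of 85% to 29% rests on the assumed ICC values, equal slum sizes and no loss.

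**What to change.** Keep the enrolment plan and replace the unqualified 80% statement with a calculation for 25 versus 25 areas and 48 degrees of freedom. State the assumed ICC and its basis, the expected number of children per slum, the expected 2-year loss, and whether 2,000 is counted before or after that loss. Then report either the power for 0.1 SD or the difference detectable with 80% power, for example about 0.13 SD at ICC 0.01 or 0.15 SD at ICC 0.02, each with 20% loss. Retain 80% at 0.1 SD only if the stated ICC and loss support it. If the investigators already hold an ICC low enough, stating it with the loss allowance settles the matter.

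The cost is wording only. No child or slum need be added to make the statement accurate. The downside is that the stated figure may become less favourable.

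### The baseline chi-square test counts children as independent although slums are randomised, and the one-value-per-area rule is not written for the change in prevalence of undernutrition

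*Protocol*

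**What the plan says.** The unit of allocation is clear. Under Unit of randomization the protocol states "Randomization will be by the urban slums", and under Setting that "50 slums will be randomly allocated, 25 to each of the two arms of the trial".

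Sample Size and Data Analyses then describes four kinds of comparison:

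- **Baseline.** "Univariate analyses will be done to compare age, sex and history of passage of worms and weight and height in 25 control areas" and in the 25 albendazole areas, "using the chi square test for categorical" variables and Student's t test for continuous ones. No adjustment for clustering is named.
- **Weight and height gain, the main outcomes.** Because areas are randomised, gains are assessed by area with one value for each, and the 25 areas of one arm are compared with the 25 of the other at one and two years.
- **Subgroups.** "weight and height gains will be calculated for children who are underweight, stunted and wasted at enrollment in the control and ABZ groups". No test and no unit is given.
- **Prevalence of undernutrition.** "We will also compare 2-year changes in the proportion of underweight, stunted and wasted in the two groups". Again no test and no unit is given.

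The sample size of about 2000 children per arm is said to allow for a design effect, but neither that design effect nor an ICC is given.

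**The concern.** The section recognises clustering twice, in the sample size and in the analysis of gains, yet names for baseline a test that cannot respect it. The ordinary chi-square test needs a table of independent individuals and cannot be applied to one proportion per area. Used on sex or worm history, it treats some 2000 children per arm as independent when they come from 25 slums per arm. If children in the same slum resemble each other at all, it will report baseline imbalances more often than its nominal level.

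The second issue is the reach of the area rule. It is written for weight and height gain. The change in prevalence is an effect comparison, not a baseline description, and the protocol describes it as between two groups, not between two sets of areas. An analyst following the protocol literally could run it on children.

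**Working it through.** **Inputs.** From the protocol: 25 slums per arm and about 2000 children per arm, hence m = 2000/25 = 80 children per slum on average. The sample size is set "For a standardized effect size of 0.1, with a power of 80% and an alpha level of 0.05", two-sided. Assumed: ICCs of 0.01, 0.02 and 0.05, since the protocol gives none, and equal slum sizes.

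**1. The protocol's own figure.** Without clustering, n per arm = 2(1.960 + 0.8416)²/0.1² = 2 × 7.849/0.01 = 1570. The stated 2000 therefore implies a design effect (DE) of 2000/1570 = 1.274, if clustering is the only inflation. From DE = 1 + (m − 1) × ICC, the implied ICC is 0.274/79 = 0.0035. The figure of 2000 can be neither confirmed nor refuted, because the design effect used is not stated.

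**2. True error of a child-level test of a baseline variable.** Clustering multiplies the variance of the difference between arms by DE, and the test does not know it. A nominal 5% test then rejects with probability 2[1 − Φ(1.96/√DE)].

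| ICC | DE at m = 80 | 1.96/√DE | True error |
|---|---|---|---|
| 0.0035 (implied) | 1.274 | 1.736 | 8.2% |
| 0.01 (assumed) | 1.79 | 1.465 | 14.3% |
| 0.02 (assumed) | 2.58 | 1.220 | 22.2% |
| 0.05 (assumed) | 4.95 | 0.881 | 37.8% |

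A t test on one value per area (25 + 25 − 2 = 48 degrees of freedom) would hold about 5% whatever the ICC.

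**3. Change in prevalence.** Two errors act here if children are the unit. Ignoring slums understates the variance by the factor DE. Treating a child's two measurements as independent overstates it: with equal variances and within-child correlation ρ, the true variance of the change is (1 − ρ) times the assumed one. The net ratio of true to assumed variance is (1 − ρ) × DE. For illustration, with ρ = 0.6 (assumed) and ICCs of the change of 0.01, 0.02 and 0.05:

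- 0.4 × 1.79 = 0.716: true error about 2%
- 0.4 × 2.58 = 1.032: true error about 5%
- 0.4 × 4.95 = 1.98: true error about 16%

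The test can therefore be conservative, about right or liberal. Stable differences between slums also cancel in a change, so an ICC for baseline levels cannot simply be carried over.

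**4. Smaller groups.** With an assumed 20 children per slum in a subgroup, DE = 1 + 19 × ICC, and a child-level test would have a true error of 5.8%, 7.2%, 9.5% and 16.0% at ICCs of 0.0035, 0.01, 0.02 and 0.05.

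**The case against.** The strongest reply is that little depends on this. The main comparison is by area, no conclusion or adjustment in the protocol rests on a baseline p-value, and details of secondary analyses may sit in a statistical analysis plan that is not at hand. It is also fair that the protocol's own figures point to about 8%, and that the 14% to 38% rests on assumed ICCs. All of this limits the importance of the point. It does not rescue the chi-square test, which is named in the protocol and is wrong for this design.

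A reader might infer more than the text supports:

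- **That the baseline t tests are child-level too.** The comparison is worded as between areas, much as for the gains, so a t test on area means is a possible reading.
- **That the prevalence and subgroup comparisons are child-level, with p-values that are too small.** Neither sentence names a unit or a test. The area rule comes just before and can be read to cover subgroup gains. The chi-square test is tied to the baseline comparison, and carrying it over to prevalence is a guess. Even then, step 3 shows that the direction of the error is not fixed.
- **That three subgroups by two outcomes give a 26% chance of a false positive (1 − 0.95⁶).** No subgroup test is announced, the three groups can overlap, and independence of weight and height gain cannot be assumed.
- **That the protocol claims a special benefit in malnourished children.** It says only that their gains will be calculated. Those gains alone could not support such a claim, which is a caution for reporting and not an error in the text.

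**Conclusion.** The point holds in a limited form. The chi-square test for baseline sex and worm history ignores the unit of randomisation, and its p-values are too small for any positive ICC. The nominal 5% becomes about 8% at the implied design effect of about 1.27, and 14% to 38% over assumed ICCs of 0.01 to 0.05 at 80 children per slum. The implied ICC comes from planning a continuous outcome, so for sex or worm history it is only a guide, and the two may cluster to different degrees.

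For the change in underweight, stunting and wasting, the protocol does not state that the comparison is by area. That wording should be closed, because a child-level test would in general have the wrong error rate, in a direction set by the ICC of the change and the within-child correlation. The comparison of weight and height gain is sound on this point.

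**What to change.** State that the area is the unit for every comparison between arms:

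- **Baseline:** summarise each variable by area within arm. Either give no test, or replace the chi-square with an area-level or cluster-adjusted test. State that any t test is on area means.
- **Underweight, stunting, wasting:** for each area, compute the change in proportion among children measured at both times, and compare the 25 values in one arm with the 25 in the other. This handles both the clustering and the pairing.
- **Subgroups:** report gains by area as estimates with confidence intervals. Claim a differential benefit only from an area-level contrast: the within-area difference in mean gain between malnourished and other children, compared between arms.

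The cost is analysis wording and somewhat wider secondary intervals. No further data are needed, and the primary comparison does not change.
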